## Abstract

**Introduction:**

Chronic pain is a common health problem that is not efficiently managed by standard analgesic treatments. There is evidence that treatment resistance may result from maladaptive brain changes in areas that are fundamental to the perception of pain. Knee osteoarthritis is one of the most prevalent causes of chronic pain and commonly associated with negative affect. Chronic knee osteoarthritis pain is also associated with altered right anterior insula functional connectivity. We posit that reversal of these brain circuit alterations may be critical to alleviate chronic pain and associated negative affect, and that this can be achieved through non-invasive neuromodulation techniques. Despite growing interest in non-invasive neuromodulation for pain relief and proven efficacy in depression, results in chronic pain are mixed with limited high-quality evidence for clinical and mechanistic efficacy. Limitations include patient heterogeneity, imprecision of target selection, uncertain blinding and protocols that may deliver pulses at subclinical efficacy.

**Methods and analysis:**

We hence developed an optimised treatment protocol of connectivity-guided intermittent theta-burst stimulation (iTBS) targeting the left dorsolateral prefrontal cortex with accelerated delivery on four consecutive days (allowing 4 days within the same week as protocol variation) with five daily treatment sessions that will be piloted in a sham-controlled design in 45 participants with chronic knee pain. This pilot study protocol will assess feasibility, tolerability and explore mechanistic efficacy through serial functional/structural magnetic resonance imaging (MRI) and quantitative sensory testing.

**Ethics and dissemination:**

This pilot trial has been approved by the Ethics Committee Cornwall and Plymouth.

Results of the pilot trial will be submitted to peer-reviewed journals, presented at research conferences and may be shared with participants and PPI/E advisors.

**Trial registration number:**

ISRCTN15404076.

Strengths and limitations of this studyThe protocol combines connectivity-guided neuronavigation for improved precision to target the prefronto-insular circuit with accelerated delivery of five daily intermittent theta-burst stimulation sessions over 4 days in 1 week for enhanced efficacy and efficiency in a sham-controlled randomized controlled trial (RCT) design.Advanced serial MRI of brain network function complements psychophysical and questionnaire outcome markers before and after transcranial magnetic stimulation protocol to explore mechanistic efficacy.Recruitment is predominantly from a research-ready community cohort which together with the single centre design may limit generalisability.The intense protocol may only be accommodated and tolerated by a subgroup of pain patients.The total number of 36 000 pulses and the permitted reduction of resting motor threshold below 80% may limit efficacy of the intervention.

## Introduction

Chronic pain is a major burden for society, economy, health systems and individuals. There is a lack of effective analgesic treatments in chronic pain with an urgent need for novel treatments. Maladaptive brain mechanisms are increasingly recognised as key contributors to the development and persistence of pain.^1^ A feature is the altered communication between brain areas that are involved in the processing of pain signals and the modulation of the associated pain perception, demonstrated by dysfunctional connectivity of the right anterior insula (rAI).^2^

These maladaptive functional brain network changes are thought (i) to drive the experience of chronic pain and central pain sensitisation, (ii) to be potentially reversible by non-invasive neuromodulation, and thus support the notion that interventions that normalise the brain’s (and in particular fronto-limbic) connectivity will also reverse central pain augmentation or associated affective experience.

Repetitive transcranial magnetic stimulation (rTMS) is a promising tool to non-invasively and focally stimulate the brain through induction of small electrical currents. Choice of stimulation protocols are thought to determine excitatory or inhibitory local and downstream effects with acute and longer-term neuromodulatory effects on targeted brain circuits. The exact mechanism of acute neuromodulatory and neuroplastic effects and the substantial interindividual and intraindividual variability are poorly understood.^3^ Clinical efficacy of rTMS is well-established for the treatment of major depression, approved by the Federal Drug Administration (FDA) in the USA and the National Institute of Clinical Excellence in the UK. In chronic pain, to date evidence for effective neuromodulation is limited to invasive protocols and selected indications.^4^ There is however considerable recent interest in non-invasive brain stimulation (NIBS) trials in chronic pain yet results to date are mixed. Meta-analyses and systematic reviews have described NIBS as having ‘poor or inconclusive’ analgesic effects across sites and pain disorders,^4–6^ ‘minimally clinically relevant’,^6^ to ‘promising’^7^ and ‘probable efficacy’ for either motor cortex (M1) or dorsolateral prefrontal cortex (DLPFC) stimulation.^8^ There are major quality concerns with most studies considered poor^4^ due to underpowered sample sizes, lack of blinding, inadequate randomisation or missing sham for comparisons. Moreover, there are uncertainties regarding the most effective brain stimulation site, type of stimulation, target population. Nevertheless, pain relief was frequently found to be >30%^9^ which encourages to seek further improvements and address limitations in order to fully assess and exploit the potential that this technology may hold for pain treatment.

To address these shortcomings we chose to target the left DLPFC as a particularly promising yet relatively understudied target site for rTMS in chronic pain due to its strong modulatory influence on the rAI, a key hub in pain processing with known altered connectivity in chronic pain.^2^ Stimulating the left DLPFC is expected to modulate the prefronto-insular pathway as a putative central pain modulatory effect. This pathway is also a key target in the clinically effective rTMS treatment of major depression suggesting a second putative beneficial effect through reduction of negative affect and related pain augmentation.

For target selection, we chose resting state functional MRI (rsfMRI) based effective connectivity to determine the coordinates within the anatomically defined left DLPFC that show the strongest effective connectivity to the rAI as in our previous work.^10 11^ In addition, recently accelerated, optimised TMS protocols were reported to be safe and similarly effective to standard rTMS using intermittent theta burst stimulation (iTBS).^12–15^ There are several advantages expected from iTBS protocols that are faster than standard rTMS and may have stronger neuroplasticity effects. Also, the multiple treatment blocks per day with 50 min intervals are expected to further enhance effectiveness and allow to deliver a higher cumulative weekly dose with the benefit of shorter overall treatment course.

Motivated by the promising results of the optimised iTBS protocol in major depression, we translated and adapted the approach to chronic musculoskeletal pain, which, if effective, would greatly improve clinical interest in this technique both for cost and practical reasons. As study population we chose knee osteoarthritis (OA) as one of the most common causes of chronic musculoskeletal pain and to avoid potential heterogeneity from different pain aetiology. Based on the known comorbidity, we anticipate that the study population of moderate chronic knee OA pain will report higher negative affect than the general population which may further increase the likelihood of neuromodulatory efficacy at the chosen target site.

This parallel, sham-controlled pilot study will investigate a 4-day (over 1 week) intense, imaging-guided iTBS protocol that is individually targeted within the left DLPFC to maximise the connectivity with the rAI. Study participants with moderately severe, chronic knee pain will undergo serial MRI, behavioural and quantitative sensory testing (QST) before and after the iTBS/sham intervention and online recording of patient-reported outcomes until week 18 to guide the protocol and sample size for future RCT interventions.

### Objectives

To test the feasibility and tolerability of an optimised accelerated 4-day (over 1 week) iTBS protocol with five daily sessions (total pulses 36 000 aimed at 80% resting motor threshold (RMT)) using connectivity-guided targeting of the left DLPFC in chronic knee OA patients with moderately severe pain.To assess the variance of mechanistic outcome markers comparing the intense iTBS protocol vs sham.To explore clinical efficacy metrics, and the feasibility of online recorded patient-reported outcome measures (PROMs) in the iTBS and sham arm.To explore the effects of iTBS on negative affect, stress and arousal between iTBS and sham.To assess feasibility of blinding using sham TMS.

## Methods and analysis

### Trial design

Single centre, sham controlled randomised mechanistic pilot study at the University of Nottingham with a parallel group study design, whereby participants will either receive active iTBS or sham iTBS with random allocation of 2:1. The uneven allocation was chosen to achieve blinding but preferencing power for statistical analyses in the active condition.

### Hypotheses

#### Primary mechanistic hypotheses

Accelerated, personalised iTBS of the DLPFC modulates *functional activity and connectivity* of brain circuits involved in central pain control in chronic musculoskeletal pain compared with sham controls. The direction of change is expected to reduce hallmark features of the pain connectome, such as reduction of the abnormally increased rAI-posterior default mode network anticorrelation.Accelerated, personalised iTBS of the DLPFC increases endogenous antinociception in chronic musculoskeletal pain compared with sham controls.

#### Secondary hypotheses

Accelerated, personalised iTBS of the DLPFC reduces pain catastrophising, anxiety and improves mood in chronic musculoskeletal pain compared with sham controls.Accelerated, personalised iTBS of the DLPFC reduces sensitivity to experimental pain at the end of the intervention compared with sham controls.Accelerated, personalised iTBS of the DLPFC reduces physiological arousal and reported stress levels compared with sham controls.

### Study procedures

Participants will first be assessed over phone for meeting safety and eligibility criteria before giving informed written consent. Participants will be asked to attend for baseline assessments (visit 1) (ca. 2 hours including MRI, and psycho-physical assessment including brief experimental pain exposure) (see figure 1). Then participants will undergo an intervention week with four visits (visit 2–5) lasting about half a day each. Each visit will consist of five blocks of iTBS or sham with inter-block interval of ~50 min during which participants will be offered refreshments and food in a comfortable waiting area before getting prepared for the next session. The sixth and final study visit is a repeat of the baseline visit, and will be scheduled within 18–72 hours of the last treatment session. This will be followed by online patient self-recording of pain and emotional outcomes up to 16 weeks.

**Figure 1 F1:**
[figure not shown]
Pilot study overview. iTBS, intermittent theta burst stimulation; QST, quantitative sensory testing.

### Recruitment and inclusion criteria

Participants will be recruited primarily from previous participants who consented to be contacted (such as the community-based Investigating Musculoskeletal Health and Wellbeing cohort)^16^ and additional recruitment pathways via posters, general practitioner surgeries and other NHS services (joint replacement waiting list) or corecruited from ongoing studies that allow corecruitment as required. Individuals who consented to be contacted about new studies, will be contacted by the study team who originally consented the participant; only if the participant then expresses interest in the new study and agrees for their contact details to be passed on to the new study team, the latter will contact them.

Participants may be initially invited to take part in the study by sending a short format participant information sheet (PIS) form that summarises the main points of the study for consideration of interest; participants who contact for further information will be sent the final PIS. Alternatively, they may find the short format PIS as a poster and contact us. Posters may be put around the Nottingham University Hospital Trust, the Medical School and other University of Nottingham sites, public sites such as public libraries and leisure/community centres. Posters may also be placed on local press, including but not limited to The Nottingham Post and Metro. The same advert may be featured on UK websites related to chronic pain, including but not limited to the Pain Centre Versus Arthritis webpages (http://www.nottingham.ac.uk/paincentre).

Participant enrolment and retention will be continually monitored, and numbers fed back at the study team meetings. Feedback from participants will be used to maintain recruitment and retention rates.

#### Inclusion criteria

18–75 years of age and able to consent.Chronic knee pain (minimum 6 months duration) with visual analogue scale (VAS) score ≥4/10.Able to accommodate the study visits without disruption to their jobs or other responsibilities and without experiencing excessive physical strain or other distress.

#### Exclusion criteria

Patients are admitted to the study if they also meet the following criteria:

No contraindication to MRI and TMS.No major medical or neurological conditions unrelated to the pain condition.Not scheduled for total knee replacement surgery within 1 month of study visits or other considerable treatment change.No change in pain medication in the past 4 weeks.Not on centrally active medication other than stable antidepressants or on opioidergic analgesic treatment.Not on medication, alcohol or recreational drugs, thought to increase risk of seizure and/or syncope.Not experiencing frequent headaches.

Participants will be reimbursed for travel expenses and provided with free drinks and food during study sessions but will not be compensated for their time.

### Transcranial magnetic stimulation

TMS will be delivered using the Magstim Horizon Performance system with StimGuide Navigated TMS package (The Magstim Co Ltd). Single-pulse TMS will be applied to the left motor cortex using a handheld figure-of-eight coil (diameter 7 cm) to determine the RMT. RMT is defined as the minimum stimulator output intensity needed to achieve a minimum motor evoked potential-amplitude of 50 μV in the completely relaxed abductor pollicis brevis-muscle in at least 5 out of 10 trials. For all treatments, the iTBS protocol will be delivered using a fixed 7 cm diameter coil (E-z Cool Coil and support arm) consisting of three pulses (aimed at 80% RMT, but may be lowered to avoid participant discomfort) of 50 Hz repeated at 200 ms (5 Hz) intervals with a total 1800 pulses per block, 9000 pulses per visit/day and 36 000 pulses in total/treatment week.

The staff operating the TMS device (SZ, senior research nurse with 3 years experience in rTMS treatment/trials; DH senior research fellow with 2 years experience in research TMS) are trained on the MAGSTIM system and adhere to all safety instructions.

### MRI acquisition

Imaging data will be acquired on a GE Premier 3T MR scanner using a 48-channel head coil (GE Healthcare, USA). Structural scans include high-resolution T1-weighted (T1w) and T2-weighted (T2w) images for the purpose of image registration. The T1w images will be acquired using 3D MPRAGE sequence (voxel size=1 mm isotropic, FOV=256, matrix=256, 256 sagittal slices, TI=800 ms, FA=8°) and T2w will be images acquired using 3D Cube T2 FLAIR sequence (voxel size=1 mm isotropic, FOV=256, matrix=256, 256 sagittal slices, TR=6300 ms, TE=121 ms, TI=1787 ms). RsfMRI data will be acquired using whole-brain 2D GE-EPI sequence (TR=1400 ms, TE=35 ms, flip angle=68°, in-plane FOV=212×212 mm, 57 slices, slice thickness=2 mm, voxel size=2 mm isotropic, hyperband factor=3, ARC factor=2, 15 min total scan time). To measure the $b_{0}$ field for correction of echoplanar imaging (EPI) distortions, we will also acquire two SE-EPI images with reversed phase encoding directions. The SE-EPI images have the same geometry, echo spacing and phase encoding direction parameters as the GE fMRI scans.

### Image processing and TMS neuronavigation

Image pre-processing follows the same procedure as that described in Pszczolkowski *et al*.^10^ In brief, the structural T1w images are brain extracted, bias corrected and segmented into white matter (WM), grey matter (GM) and cerebrospinal fluid probability maps which are binarised at a probability of 0.98 and then eroded using a spherical kernel with a radius of 2 voxels to obtain the final tissue labels. The blood oxygenation level dependent (BOLD) rsfMRI undergo EPI distortion correction, motion correction, slice timing correction, smoothing, denoising and high-pass filtering. Finally, the WM and GM tissue labels are transformed into rsfMRI BOLD space and used to regress out the WM and GM time series from the processed rsfMRI BOLD data.

For identification of the iTBS treatment target, a methodology similar to Pszczolkowski *et al*^10^ will be followed. However, in the current pilot trial the DLPFC searchlight described in Fox *et al*^17^ will be used as primary volume of interest, and the background removal procedure is based on a threshold computed automatically rather than by visual inspection. This threshold is computed as the 98th percentile of the T1w intensities within a mask of background (air) voxels around the outside of the skull in MNI space which is previously transformed into T1w space.

### Quantitative sensory testing

Central pain inhibition will be tested pre-TBS and post-TBS treatment using the psychophysical paradigm of conditioned pain modulation (CPM). The test stimulus will be pressure pain threshold (PPT) and the conditioning stimulus ischaemic pain caused by a blood pressure cuff placed at the calf of the unaffected leg. The test stimulus (PPTs) will be administered at three body sites (on the affected side), including trapezius muscle, metacarpophalageal joint of the thumb and the patella. If no preference is shown with respect to the affected side, then the patients non-dominant body side will be examined. All QST assessment are completed by DH with >10 years experience.

CPM is calculated as follows:

CPM (%)=(PPTpost-conditioning–PPTpre-conditioning)/PPTpre-conditioning×100.

Preconditioning PPTs will be used to calculate SEM and >±2×SEM to determine CPM effects in response TBS treatment.

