### Assessments

Data will be collected for the following

MRI at visit 1 and at visit 6 (pretreatment and post-treatment).QST at visit 1 and at visit 6 (pretreatment and post-treatment).

REDCap (https://www.project-redcap.org/) will be used to administer online questionnaires:

Pain characteristics

A numerical pain VAS (0–10) as online daily pain report.Weekly questionnaires:Intermittent and Constant Pain Score (ICOAP),^18^ the Central Aspects of Pain in the Knee (CAP-Knee) questionnaire.^19^At visit 1 and 6:painDETECT,^20^ Pain Catastrophizing Scale (PCS),^21^ ICOAP,^18^ General Anxiety Depression scale (GAD-7),^22^ Depression Anxiety Stress Scales (DASS-21),^23^ Hospital Anxiety and Depression Rating-Scale (HADS),^24^ Patient Health Questionnaire (PHQ-9),^25^ CAP-Knee,^19^ Montreal Cognitive Assessment test.^26^

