### Outcome measures

#### Primary

Variance of changes in pre-selected neuroimaging functional markers of the descending pain modulatory system at final versus baseline visit.Variance of change in CPM (pain intensity change with/without conditioned pain stimulus) at final versus baseline visit.Number of participants recruited and retained on the trial.Number of iTBS sessions completed at 80% RMT.

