### Sample size

The pilot aims to recruit n=45 (30 active, 15 sham iTBS) participants. In this pilot study, we estimate the variance of the outcome measures, and adjust for the upper confidence level.^27^

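### The ±2×SEM limit for a CPM response is built from preconditioning PPTs alone and omits part of the error of a CPM change; separately, the primary CPM outcome is described on a different scale from the CPM formula.

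*Protocol article*

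**What the plan says.** Under Quantitative sensory testing, the protocol article makes the test stimulus a PPT, measured at three body sites, and defines "CPM (%)=(PPTpost-conditioning–PPTpre-conditioning)/PPTpre-conditioning×100". It then gives a decision rule: "Preconditioning PPTs will be used to calculate SEM and >±2×SEM to determine CPM effects in response TBS treatment".

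The Assessments section places sensory testing at visits 1 and 6, before and after treatment. The primary outcome list gives the corresponding outcome as "Variance of change in CPM (pain intensity change with/without conditioned pain stimulus) at final versus baseline visit".

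The Sample size section says "The pilot aims to recruit n=45 (30 active, 15 sham iTBS) participants" and gives the pilot's purpose as estimating the variance of the outcome measures.

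The article gives no value or reliability for SEM. It does not say:
- whether SEM is a standard error of measurement or of a mean;
- whether it is a within-session or between-visit figure;
- whether the limit is meant for one visit's CPM or for the change between visits;
- how the three sites are combined.

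**The concern.** There are two separate problems.

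**The limit does not match the quantity it judges.** A limit of two standard errors of measurement gives roughly 5% two-sided error only when the judged quantity is a single reading with that error. A CPM value is built from two PPTs. A response to treatment, taken from visit 1 to visit 6, is built from four. No post-conditioning error enters the limit. It is also expressed in pressure units, whereas CPM is a percentage, and no conversion is stated. If individuals are classed as changed by this rule, some unchanged participants in both arms will be counted. That blurs the comparison with sham and could pass for modulation if the active arm were read alone.

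**The primary outcome is described in two ways.** The sensory testing section makes CPM a percentage change in a threshold. The outcome list makes it a change in pain intensity. Pain inhibition raises a threshold but lowers an intensity rating, so both scale and sign differ. The variance of this change is a primary outcome, so it must be clear which variance is estimated.

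**Working it through.** The article states no error rate for the rule, so there is no figure of its own to reproduce. The check is error propagation.

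**Inputs from the article**
- Limit: ±2×SEM, with SEM from preconditioning PPTs (Quantitative sensory testing).
- PPTs per CPM value: 2, pre- and post-conditioning (same section).
- Testing visits: 2 (Assessments), so the change in CPM uses 2 × 2 = 4 PPTs per site.
- Participants: 30 active and 15 sham (Sample size).

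**Assumptions, not in the article**
- SEM is the standard error of measurement of one PPT at one site, put on the same relative scale as CPM.
- The PPT errors are normal with equal SD.
- There is no true change.
- The errors are independent at first; this is relaxed below.

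**Step 1: independent errors.** A sum or difference of k PPTs has SD = SEM × √k. The share beyond the limit is P = 2 × [1 − Φ(2/√k)].

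| Quantity judged | k | SD | Limit in SDs | P |
|---|---|---|---|---|
| One PPT | 1 | SEM | 2 | 4.6% |
| CPM at one visit | 2 | 1.41 × SEM | 1.41 | 15.7% |
| Change in CPM, visit 6 − visit 1 | 4 | 2 × SEM | 1 | 31.7% |

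For CPM at one visit, no true change means no true CPM effect.

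The rule is two-sided, so half of the 31.7%, about 15.9%, is apparent improvement and half apparent worsening. In the active arm this is 30 × 0.317 = 9.5 participants, about 4.8 in each direction.

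**Step 2: percentage scale.** Step 1 treats CPM as a plain difference. The percentage formula was simulated with 1,000,000 draws, a PPT error of 5% to 20% of the true value, and a limit of twice that error. For the change in CPM it gave 32–34% when true CPM is 0 and 39–40% when true CPM is 30% at both visits. Dividing by the preconditioning value does not bring the rate down.

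**Step 3: correlated errors.** If SEM is a between-visit figure, error shared by the two PPTs of one session inflates SEM but cancels within CPM. With same-session error correlation ρ, SD(change) = 2 × SEM × √(1 − ρ), so P = 2 × [1 − Φ(1/√(1 − ρ))].

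| ρ | SD of change / SEM | P |
|---|---|---|
| 0 | 2.00 | 31.7% |
| 0.2 | 1.79 | 26.4% |
| 0.3 | 1.67 | 23.2% |
| 0.5 | 1.41 | 15.7% |
| 0.7 | 1.10 | 6.8% |
| 0.8 | 0.89 | 2.5% |

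The nominal 4.6% is met only where 1/√(1 − ρ) = 2, that is ρ = 0.75.

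**Step 4: limits that match the quantity.** Under independence, a two-sided 5% limit is 1.96 × √2 × SEM = 2.77 × SEM for one visit's CPM and 1.96 × 2 × SEM = 3.92 × SEM for the change.

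**Step 5: the two definitions side by side.** In the sensory testing section the measured quantity is a threshold, the unit is per cent of the preconditioning value, and inhibition is positive. In the outcome list the quantity is pain intensity, the comparison is with and without the conditioning stimulus, and inhibition is a decrease. This conflict needs no assumption about error.

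**The case against.** The strongest reply is that the rule does not touch what the pilot reports as primary. The listed outcome is the variance of a continuous change, and no responder count appears among the primary or secondary outcomes. The mechanistic hypotheses are comparisons with sham. This stands: the limit can distort individual classification, but not the variance estimate. A reader might infer that a primary outcome carries a high false responder rate; the article does not support that.

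The second reply is that 31.7% rests on several unstated assumptions. This also stands. The rule follows the within-visit formula and could be read as applying to one visit's CPM (15.7%). A single-site SEM applied to the mean of three sites with independent errors gives 8.3%. Correlation within a session lowers the rate further. Nor is 31.7% a floor: preconditioning PPTs exist at both visits, so SEM may already contain between-day variation. A count of anyone beyond the limit at any of three sites would give 68.2% with independent errors, but the article describes no such count.

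The third reply is that a condensed article may leave the derivation of SEM, its units and the handling of sites to the full protocol or analysis plan, and that pressure units convert easily to a percentage of baseline. This is fair for those details. It does not cover the source of the limit, which the article fixes as preconditioning PPTs only, or the two conflicting descriptions of CPM. Both are stated text.

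**Conclusion.** The point holds in two parts.

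First, a ±2×SEM limit from preconditioning PPTs does not carry the error of a CPM value or of its change between visits. If SEM is the measurement error of one PPT and errors are independent, two-sided false classification is 15.7% for one visit's CPM and 31.7% for the change, against a nominal 4.6%. With a between-visit SEM and same-session correlation of 0.2 to 0.8, the rate for the change is 26.4% to 2.5%. A reader might conclude that about a third of unchanged participants will be misclassified. That is one end of a conditional range, and only half of it would look like benefit. The article gives no SEM, reliability or correlation with which to place the trial in that range. The rule could reach its nominal rate, but only if the correlation happened to be near 0.75.

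Second, and without any such assumption, the primary CPM outcome is described as a change in pain intensity while the method measures a threshold and reports a percentage. Scale and sign differ, so it is unclear which variance the pilot estimates. This part reaches a primary outcome; the first part reaches only the classification of individuals.

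**What to change.** - In the primary outcome list, replace the parenthesis after CPM with the PPT-based CPM (%) of the Quantitative sensory testing section, so that scale and sign agree.
- Keep the continuous visit 6 minus visit 1 change in CPM as the outcome.
- If individual changes are classified, state the quantity judged, what SEM means, its scale and how sites are combined. Base the limit on the error of the CPM change itself, on the CPM scale. One option is ±1.96 × the SD of CPM change in the sham arm.
- Use ±3.92×SEM only if the four errors can be taken as independent. It is too strict otherwise: at ρ = 0.5 the SD of the change is 1.41 × SEM, so the limit lies at 3.92/1.41 = 2.8 SDs.

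The cost is wording only, with no new data. Where the present limit is too narrow, fewer participants will be classed as changed. The sham-based limit is imprecise: with 15 participants the 95% limits for an SD run from about 0.73 to 1.58 times the estimate. It also includes any real response to sham. Both should be said when it is used.
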